## Abstract

**Background:**

Fetal growth restriction (FGR) is a serious obstetric condition for which there is currently no treatment. The EVERREST Prospective Study has been designed to characterise the natural history of pregnancies affected by severe early onset FGR and establish a well phenotyped bio-bank. The findings will provide up-to-date information for clinicians and patients and inform the design and conduct of the EVERREST Clinical Trial: a phase I/IIa trial to assess the safety and efficacy of maternal vascular endothelial growth factor (VEGF) gene therapy in severe early onset FGR. Data and samples from the EVERREST Prospective Study will be used to identify ultrasound and/or biochemical markers of prognosis in pregnancies with an estimated fetal weight (EFW) <3rd centile between 20+0 and 26+6 weeks of gestation.

**Methods:**

This is a 6 year European multicentre prospective cohort study, recruiting women with a singleton pregnancy where the EFW is <3rd centile for gestational age and <600 g at 20+0 to 26+6 weeks of gestation. Detailed data are collected on: maternal history; antenatal, peripartum, and postnatal maternal complications; health economic impact; psychological impact; neonatal condition, progress and complications; and infant growth and neurodevelopment to 2 years of corrected age in surviving infants. Standardised longitudinal ultrasound measurements are performed, including: fetal biometry; uterine artery, umbilical artery, middle cerebral artery, and ductus venosus Doppler velocimetry; and uterine artery and umbilical vein volume blood flow. Samples of maternal blood and urine, amniotic fluid (if amniocentesis performed), placenta, umbilical cord blood, and placental bed (if caesarean delivery performed) are collected for bio-banking. An initial analysis of maternal blood samples at enrolment is planned to identify biochemical markers that are predictors for fetal or neonatal death.

**Discussion:**

The findings of the EVERREST Prospective Study will support the development of a novel therapy for severe early onset FGR by describing in detail the natural history of the disease and by identifying women whose pregnancies have the poorest outcomes, in whom a therapy might be most advantageous. The findings will also enable better counselling of couples with affected pregnancies, and provide a valuable resource for future research into the causes of FGR.

**Trial registration:**

NCT02097667 registered 31^st^ October 2013.

**Electronic supplementary material:**

The online version of this article (doi:10.1186/s12884-017-1226-7) contains supplementary material, which is available to authorized users.

## Background

Fetal growth restriction (FGR) is a serious condition affecting about 8% of all pregnancies and contributing to 30% of stillbirths [1]. As yet there is no therapy that improves fetal growth in utero, thus current management is to deliver the fetus before intrauterine death or irreversible organ damage occurs [2]. This is particularly challenging in early onset FGR, where delivery adds additional risks to the baby from extremely preterm birth, with its own attendant short and long-term complications [3–5]. Furthermore FGR may be detected when the estimated fetal weight (EFW) is below 500 g, a situation considered by many to be non-viable. FGR is most commonly due to three principal factors: a) maternal diseases such as infections; b) fetal chromosomal, genetic, or structural anomalies; and, most often, c) placental insufficiency. Placental insufficiency manifests as inadequate uteroplacental blood flow on ultrasound scan and maternal vascular malperfusion (MVM) on placental histology [6].

We are currently developing a treatment for FGR caused by placental insufficiency [orphan designation EU/3/14/1415], using maternal adenovirus gene therapy to increase expression of vascular endothelial growth factor (VEGF) protein in the uterine arteries. VEGF is secreted by the placenta, induces vasodilatation, and mediates vasculogenesis and angiogenesis [7, 8]. In FGR, however, maternal serum levels of VEGF are significantly lower than in normal pregnancy [9, 10]. Previous studies in normal sheep pregnancy show that administering adenovirus VEGF gene therapy (Ad.VEGF) into the maternal uterine arteries increases uterine artery blood volume flow long-term, causes nitric oxide release and relaxes the vessels [11–13]. Further studies in sheep and guinea pig models of FGR have shown that administering Ad.VEGF gene therapy into the maternal uterine arteries safely increases fetal growth [14, 15].

The EVERREST Consortium plans to carry out a phase I/IIa trial to assess the safety and efficacy of maternal uterine artery injection of Ad.VEGF in women with pregnancies affected by severe early onset FGR. This will be called the EVERREST Clinical Trial. For the first-in-woman trial of maternal gene therapy the eligibility criteria will be designed to identify severely affected pregnancies, where the balance of risk and potential benefit is most favourable. These pregnancies will naturally have high rates of maternal, fetal, and neonatal complications. The safety and efficacy of the intervention in the trial pregnancies will need to be compared with data from a cohort of similar severely affected pregnancies that do not undergo intervention.

Several prospective cohort studies have investigated the outcomes of pregnancies where the fetus was found to be small in mid-pregnancy [16–21]. Recent outcome data have also been provided by the Trial of Umbilical and Fetal Flow in Europe (TRUFFLE), a randomised controlled trial comparing different indications for delivery in pregnancies diagnosed with severe FGR from 26 weeks of gestation onwards [22, 23]. However, none of these studies includes the level of detailed maternal, fetal, and infant outcome data required to properly assess safety in the EVERREST Clinical Trial [24]. A detailed study of the natural history of pregnancies affected by severe early onset FGR is therefore required.

The EVERREST Prospective Study will clinically and biochemically characterise a cohort of pregnancies affected by severe early onset FGR across the four European centres that will be taking part in the EVERREST Clinical Trial. A database will be created containing information about antenatal investigations, maternal complications, fetal outcome and neonatal progress. This will be linked to a bio-bank containing samples including maternal blood and umbilical cord blood as well as tissue from the placenta, placental bed, and the myometrium. These samples will be used to investigate the natural history and biological mechanisms which underlie severe early onset FGR and, in conjunction with the database, will be used to investigate potential biomarkers for fetal and neonatal outcome.

## Methods

### Aims

To characterise the natural history of pregnancies affected by severe early onset FGR in order to:Provide up-to-date knowledge for clinicians and future patients.Interpret the safety of maternal growth factor gene therapy in a future clinical trial.
To establish a bio-bank of well phenotyped samples that can be used to investigate the biological mechanisms underlying severe early onset FGR.To identify ultrasound and/or biochemical markers of prognosis in pregnancies with an EFW <3rd centile between 20+0 and 26+6 weeks of gestation.

### Design

This is a 6-year European multicentre prospective cohort study. The design and publication of this protocol has been performed in line with the ‘strengthening the reporting of observational studies in epidemiology’ (STROBE) guidelines [25, 26].

### Study population

#### Inclusion criteria

Live singleton fetus.Estimated fetal weight <600 g and <3rd centile for gestational age as defined by local criteria.Gestational age at diagnosis 20+0 to 26+6 weeks of gestation, based on ultrasound and/or last menstrual period.Informed consent given by the participant and signed consent form completed.

#### Exclusion criteria

Multiple pregnancy.Maternal age under 18 years.Known abnormal karyotype at enrolment.Known major fetal structural abnormality at enrolment defined as a lethal, incurable or curable severe abnormality with a high risk of residual handicap [27].Indication for immediate delivery.Women who lack the capacity to give informed consent.Any medical or psychiatric condition which compromises the woman’s ability to participate.Maternal HIV or hepatitis B or C infection.Premature preterm rupture of membranes before enrolment.

#### Study setting

Participants are recruited from University College Hospital London, University Medical Centre Hamburg-Eppendorf, Maternal-Fetal Unit Hospital Clinic Barcelona, and the Skane University Hospital, Lund. All four sites are tertiary referral centres for their surrounding area, performing 12,000 to 20,000 fetal ultrasound scans per year.

### Study procedures

The study timeline is shown in Fig. 1.

**Fig. 1 Fig1:**
[figure not shown]
Participant timelines for the EVERREST Prospective Study

#### Data collection

In order to fully characterise this cohort, an extensive data set is collected for each participant. This includes, but is not limited to, the majority of the optimal data set recommended by the Global Pregnancy CoLaboratory (COLAB) [28]. At enrolment maternal demographic, medical, obstetric, social, and family history are collected, as well as paternal demographic and family history and details of previously fathered pregnancies. Data are collected on the current pregnancy, including the results of ultrasound scans before and after enrolment, screening tests, invasive tests, and tests for maternal infection.

Data are collected about maternal antenatal, perinatal, and postnatal complications. Perinatal data are collected about the delivery, any maternal medication, the condition of the newborn and any need for resuscitation. For liveborn infants, data are collected at 4, 24 h, and 7 days of life as well as at discharge from the Neonatal Unit, if applicable. This includes data on cardiovascular, metabolic and respiratory status, growth, feeding, cranial ultrasound findings, retinopathy screening, and any medical or surgical complications. Surviving infants and children undergo neurodevelopmental follow-up until 2 years of age (corrected for prematurity, Table 1). Detailed health economic data are collected at approximately 6 weeks and 6 months post-delivery, including maternal and infant health service use and personal financial costs.

**Table 1 Tab1:** EVERREST Prospective Study infant neurodevelopmental follow-up plan

Age (corrected for prematurity)	3 months	6 months	12 months	24 months
Growth and health	X	X	X	X
Prechtl video assessment	X			
Amiel Tison neurological assessment, hearing, vision, and general assessment of development	X	X		
Hammersmith neuroassessment			X	X
Bayley III			X	X
Gross Motor Function Classification System (GMFCS)				X
Manual Ability Classification System (MACS)				X

All data are entered onto a central MACRO database using the participant’s unique Participation Identification Number. This password protected database is stored on servers based at University College London, which are protected by thorough electronic and physical security measures. Within the database electronic Case Report Forms include internal data checks for validity and consistency, and regular data checks are performed by the EVERREST Study Manager.

#### Ultrasound measurements

The timing of ultrasound scans is determined clinically, with fetal biometry recorded on the database no more than once a week. All ultrasound measurements are performed according to a Standard Operating Procedure (SOP, see Additional file 1). Fetal biometry includes head and abdominal circumference, both measured using an ellipse, and femur length, all measured according to the guidelines of the International Society of Ultrasound in Obstetrics and Gynecology (ISUOG) [29]. Doppler ultrasound measurements are performed with the Doppler gate across the whole width of the vessel, the angle of insonation below 30°, with measurements taken from three or more consecutive uniform waveforms. Pulsatility index (PI) is recorded for the umbilical artery (from a free-floating portion), the middle cerebral artery, and the ductus venosus. End-diastolic flow in the umbilical artery and the a wave of the ductus venosus are characterised as positive, absent, or reversed. Uterine artery volume blood flow is measured after the participant has been resting for at least 20 min. Each uterine artery is visualised using power Doppler, using the minimum power setting needed to delineate the vessel walls. The vessel diameter is measured perpendicular to the vessel during systole, between the outer aspects of the lumen, and the waveform is recorded to measure time averaged mean (TAMEAN), PI, and to define the presence or absence of notching as described [30]. Umbilical vein volume blood flow is recorded from an intra-abdominal section of the umbilical vein, with the TAMEAN recorded with the angle of insonation as close as possible to 0° and the vessel diameter measured perpendicular to the lumen, between the inner aspects of the vessel walls [31].

Because neither uterine artery volume flow nor umbilical vein volume flow are routinely performed in any of the centres, a validation system has been established for these measurements. Within each site the local ultrasound lead reviews images taken by all members of staff performing EVERREST study measurements, both when they first scan a study patient and then annually thereafter. These images are scored according to predefined criteria, with further training and review if images are unsatisfactory. Once a year the local ultrasound lead must submit three sets of assessed images, along with the score they gave to each, to the study ultrasound lead for review.

#### Sample collection

Sample collection and processing procedures are performed according to the laboratory manual and SOPs. Maternal blood is collected at enrolment and delivery for plasma, citrated plasma, serum, RNA (PAXgene® tube), full blood count, renal and liver function, and lactate dehydrogenase. At enrolment maternal whole blood is stored for DNA. Maternal urine is collected at enrolment and delivery with aliquots of whole urine, urine centrifuged at slow and fast speeds, and the pellet from centrifugation. Any excess amniotic fluid from amniocentesis is also stored. At delivery umbilical cord blood is collected for arterial and venous gases, blood spot cards, plasma, and serum (assuming sufficient volume can be collected). Placental samples are collected from two areas of the placental parenchyma, each midway between the cord insertion and the margin in areas free from macroscopic infarcts. From each area full thickness samples are collected for histological analysis, and samples from the placental villous parenchyma (maternal and fetal surfaces removed) snap frozen and/or stored in RNALater®. For women undergoing delivery by caesarean section a placental bed biopsy is also collected and processed for histological analysis.

#### Participant experience

A recent amendment in the UK has extended the study to explore the impact on women of experiencing a pregnancy complicated by early onset FGR and of participating in research during pregnancy. At enrolment women are asked to complete the state section of the State-Trait Anxiety Inventory (STAI) [32]. This is repeated at 6–12 weeks postnatally, along with the Edinburgh Postnatal Depression Scale (EPDS) [33] and the 2008 version of the Perinatal Posttraumatic Stress Disorder Questionnaire (PPQ) [34]. In addition, all study participants who have consented to ongoing contact with the study have been invited to take part in a semi-structured qualitative interview sub-study and to complete a modified version of the Reactions to Research Participation Questionnaire (RRPQ) [35].

### Sample analyses

Three initial analysis strategies are planned for maternal blood samples taken at study enrolment:Targeted angiogenic and anti-angiogenic markers: soluble FMS-like tyrosine kinase 1 (sFlt-1) and placental growth factor (PlGF) will be measured using the Roche Elecsys® automated electrochemiluminescence assay, VEGF-A, VEGF-D, soluble VEGF receptor-2, soluble endoglin, and neuropilin 1 will be measured using R&D Systems enzyme-linked immunosorbent assays (ELISAs).Semi-targeted vascular markers: 92 serum analytes implicated in cardiovascular disease will be measured on the Olink ProSEEK platform, using DNA primer-tagged antibody pairs in a proximity extension assay to provide very sensitive (1 uL serum) and specific measurements.Non-targeted proteomic analysis: a mass spectrometry-based serum profiling approach will be employed for the discovery of potential new biomarkers. Serum samples will be pooled into good and poor outcome groups and subjected to an established proteomic profiling workflow involving immunodepletion of the 12 most abundant serum proteins, tryptic digestion, 6-plex tandem mass tagging (TMT), and two-dimensional liquid chromatography (high and low pH reversed-phase) linked to quantitative tandem mass spectrometry. Candidate selection from the combined dataset will be based on standard statistical tests of fold-change, MS data quality and known function. Selected candidates will be further verified in the individual discovery samples using commercial ELISAs.

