### Statistical analysis

Characterising the natural history of severe early onset FGR (Aim 1) will involve descriptive statistical methods, including means for numerical variables and proportions for binary or categorical variables. An initial analysis is planned for the first 65 study participants to help refine the inclusion criteria for the EVERREST Clinical Trial.

The association between individual factors and outcome will be analysed using t tests and chi-squared tests, and non-parametric tests used if required (Mann–Whitney U tests and Fisher’s exact tests). Logistic regression modelling will be used to investigate whether individual and combinations of factors can be used to estimate poor outcome (primary endpoint). These factors include ultrasound findings, levels and ratios of angiogenic factors, and potential markers identified through the semi-targeted and proteomic approaches. Due to the relatively small sample size, a forward selection algorithm will be employed, and it is likely that each model will only sustain a maximum of two or three independent variables. Models will be tested for goodness of fit and discrimination using leave-one out cross validation and bootstrapping.

Survival analysis, including Cox proportional hazards regression, will be used to investigate the predictive value of individual and combined factors for the secondary outcome measure of time until the end of pregnancy.

An a priori sample size calculation is not provided, as there is currently no reliable data on expected means and standard deviations of candidate markers within such a cohort, and no data on whether and how these would differ by outcome. Within our current sample of 65, with 5 withdrawals and 18 poor outcomes, there is a ratio of good to poor outcomes of 2.33. This sample will give an 80% power to detect a standardised effect size of 1.0 to a significance level of 0.05 [36]. The potential for type 1 error, given the multiple comparisons, or type 2 error, given the small sample size, will be borne in mind when interpreting the study results.

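### Proteomic candidates are picked by outcome and verified in the same women's serum, so chance differences can pass verification and reach a prognostic model whose internal validation cannot correct for it

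*Protocol article*

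**What the plan says.** The Sample analyses section of the Protocol article lists three initial strategies for maternal blood taken at enrolment. The third is an untargeted mass spectrometry screen, and its steps are fixed in the text:

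- Discovery contrast: "Serum samples will be pooled into good and poor outcome groups".
- Selection: "Candidate selection from the combined dataset will be based on standard statistical tests of fold-change, MS data quality and known function".
- Verification: "Selected candidates will be further verified in the individual discovery samples using commercial ELISAs".

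The Statistical analysis section then lists, among the factors offered to logistic regression for poor outcome, "potential markers identified through the semi-targeted and proteomic approaches". On model building it says that "a forward selection algorithm will be employed, and it is likely that each model will only sustain a maximum of two or three independent variables". On checking it says: "Models will be tested for goodness of fit and discrimination using leave-one out cross validation and bootstrapping". No separate group of women is named for the proteomic candidates. On multiple comparisons, the section says only that the possibility of type 1 error will be kept in view when results are interpreted.

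**The concern.** Candidates are chosen because the women with poor outcomes differ from the women with good outcomes. Verification then asks whether the same women still differ when the same serum is measured by another method. If the difference arose by chance in who happened to be sampled, it is present in the serum itself, and a good second assay will find it again. The step tests the measurement. It does not test whether the protein predicts outcome.

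The same women then supply the regression data. Forward selection can be repeated inside a leave-one-out or bootstrap loop. The mass spectrometry selection cannot, because it was made once, from physical pools that contain every discovery woman, including the one left out. A protein with no prognostic value could therefore appear both verified and cross-validated.

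At stake is the third aim, prognostic markers. The Discussion expects such markers to help refine eligibility for later phase trials, support counselling and guide management.

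**Working it through.** **The plan's own figures.** The Statistical analysis section states: "Within our current sample of 65, with 5 withdrawals and 18 poor outcomes, there is a ratio of good to poor outcomes of 2.33". This reproduces: 65 − 5 = 60, 60 − 18 = 42, and 42/18 = 2.33. It also states: "This sample will give an 80% power to detect a standardised effect size of 1.0 to a significance level of 0.05". This does not reproduce. The noncentrality is 1/√(1/18 + 1/42) = 3.55, and Φ(3.55 − 1.96) = Φ(1.59) = 94%, two-sided. That is a separate matter, and nothing below depends on it.

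**Inputs.** From the article: selection by outcome pools, ELISA in the discovery samples, a 6-plex tag, and 18 poor and 42 good outcomes. Not in the article, hence assumed: the number of women pooled, three pools per group, 200 to 1000 proteins, ten candidates, the assay correlation, and a pass rule of two-sided p<0.05 in the same direction. No protein is related to outcome in any scenario.

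**Hand calculation.** Let z be a protein's standardised difference in discovery, and r the correlation between the discovery and ELISA differences in the same women. With no true effect:

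P(pass | z) = 1 − Φ((1.96 − r·z)/√(1 − r²))

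Take ten of 500 proteins, ranked by |z|.

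- The selected fraction is 0.02, so the cut-off is |z| = 2.326.
- The mean selected |z| is 2φ(2.326)/0.02 = 2.665.
- With r = 0.7: (1.96 − 0.7 × 2.665)/√0.51 = 0.132, so about 45% pass.

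Take ten of 200 proteins.

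- The cut-off is 1.96 and the mean selected |z| is 2.338.
- With r = 0.7: (1.96 − 1.637)/0.714 = 0.453, so about 33% pass.

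In independent women r = 0, and the pass rate is 0.05/2 = 2.5% whatever was selected. Group sizes do not enter the formula, so pooling only a subset does not remove the problem.

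**Simulation, main range.** Three pools per group were used, with pool technical SD 0.15 and the top ten by fold-change. ELISA correlated 0.6 to 0.8 with the serum level that mass spectrometry picks up, and there were 200 or 500 proteins. Same-sample pass rates were about 20% to 46% for 18 against 42 women. They were nearly the same, up to about 49%, for 9 against 21. In independent women the rate was about 2.5%.

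**Simulation, wider range.** Here there were 18 against 42 women and 150 cohorts per setting. Pooled discovery required p<0.05 between pools, then took the ten largest differences. The last column is the leave-one-out AUC of a two-marker linear discriminant, standing in for the logistic model, with candidate selection outside the loop. The true AUC is 0.50.

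| Proteins | Assay correlation | Pass, same women | Leave-one-out AUC |
|---|---|---|---|
| 200 | 0.5 | 14% | 0.68 |
| 200 | 0.7 | 26% | 0.72 |
| 200 | 0.9 | 37% | 0.74 |
| 500 | 0.5 | 23% | 0.73 |
| 500 | 0.7 | 39% | 0.75 |
| 500 | 0.9 | 67% | 0.78 |
| 1000 | 0.5 | 29% | 0.74 |
| 1000 | 0.7 | 50% | 0.78 |
| 1000 | 0.9 | 87% | 0.81 |

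Selecting from individual rather than pooled samples gave 18% to 89%. Across both schemes, independent women gave 2% to 3%, and at least one chance candidate passed in 70% to 100% of cohorts.

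**The case against.** The strongest reply is that the article does not overclaim. It presents initial strategies for potential biomarkers, says openly which samples are used, and does not call the step validation or replication. Moving from pooled mass spectrometry to individual ELISA is a normal measurement check. It can remove labelling and pooling artefacts, or a difference driven by one extreme sample. All of that stands. It does not settle the matter, because the Statistical analysis section passes the markers on to the model with no intervening test of association in other women.

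The article also has safeguards: models of two or three variables, leave-one-out, bootstrapping, and a caution about type 1 error. These limit overfitting in the model-building step. They do not reach the earlier selection from pools, and the caution is not a procedure.

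Three stronger readings are tempting, and the text does not support them.

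- *All 60 women are in the pools.* The 18 and 42 come from the power paragraph, and Sample analyses gives no number. If only some women were pooled, the regression would include others.
- *The markers will never be tested elsewhere.* The article is silent on this. It describes initial work in a 6-year study with a bio-bank for ongoing research, and a condensed article may leave a validation plan to the full protocol.
- *Chance findings generally pass, or the markers found will be false.* The rates are for proteins with no effect, under assumed inputs. Selection also uses data quality and known function, which were not simulated. The direction of the bias is firm, but its exact size is not.

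**Conclusion.** The concern holds as a fault in a stated rule, not as a missing detail. Followed as written, the text selects on outcome, verifies in the same women and checks the model by methods that cannot undo that selection. The result is an inflated impression of prognostic value.

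Under the main illustrative assumptions, about 20% to 49% of chance candidates pass same-sample ELISA, roughly 8 to 20 times the 2.5% expected in independent women (20/2.5 = 8; 49/2.5 = 19.6). Every scenario tried exceeded the independent rate several-fold. The figures rest on the assumed protein count, assay correlation, pool layout, candidate number and pass rule.

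The fault is confined to the proteomic strand. It does not touch the angiogenic markers named in advance, the descriptive aim or the bio-bank.

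**What to change.** 1. In Sample analyses, call the ELISA in discovery samples technical verification only, and state how many women and which samples enter the pools.
2. Before a protein is called prognostic, test it in enrolled women whose serum was not in the discovery pools, whether unused current participants or later ones. Fix the direction of effect and the test beforehand.
3. In Statistical analysis, report association and model discrimination for proteomic markers from those women only. Label any estimate that includes discovery women as exploratory and optimistic.

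The cost is additional ELISAs on banked enrolment serum, a wait for later outcomes, and a less favourable and less precise performance estimate, because the independent set may hold few poor outcomes. At the observed 18/60 = 30%, a set with another 18 poor outcomes needs about 18/0.30 = 60 further analysable women. The article gives no final sample size, so whether that number will be available cannot be judged from it.
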